## Sample size

1. **Sample Size**

| OJS plus SMS group | Placebo group | Total |
| --- | --- | --- |
| 69 | 69 | 138 |

1. **Rationale**

Based on our previous study results, we calculated a sample size of 138 (69 participants for each group) for this trial (16). The calculation was conducted to test the difference in the change in CDS from baseline (week 0) to post-dosing of OJS plus SMS (week 6) compared with the placebo. In our preliminary clinical trial, the mean difference between the two groups was found to be 0.75 and the standard deviation was 1.4. We assumed the power to detect the difference to be 0.8, the two-sided significance level to be 0.05, and a dropout rate of 20% to determine the sample size.

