# Trial Design

## Procedure

This study is a randomized, double-blind, placebo-controlled, parallel, multi-center, investigator-initiated clinical trial to assess the efficacy, safety, and economic value of OJS plus SMS compared to placebo in patients with GERC. The trial will be conducted at five hospitals in South Korea: Kyung Hee University Korean Medicine Hospital, Gangdong Kyung Hee University Korean Medicine Hospital, Daejeon University Daejeon Korean Medicine Hospital, Pusan National University Korean Medicine Hospital, and Catholic Kwangdong University International St. Mary's Hospital. After participants voluntarily signed a written informed consent, they will be screened for eligibility assessment, and those who meet the inclusion criteria will be enrolled for the next 8 weeks of the trial period (Fig.1). A total of 138 participants will be enrolled in this study from January, 2024. Participants will be allocated to either the OJS plus SMS group or the placebo group in a 1:1 ratio and will be asked to administer the investigational medicine three times a day for 6 weeks. For the evaluation of efficacy, safety, and economic assessments, participants will visit every 2 weeks until the last follow-up visit on week 8.

[figure not shown]

<임상시험 진행 흐름>

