## Efficacy Outcome Measures

### Primary Efficacy Outcome

#### Cough symptom score (Cough diary)

The CDS is a subjective cough score questionnaire that assesses the severity and frequency of cough on five scales (0 to 4) during the daytime and nighttime ^18^. The cough severity scale is divided into 0: none, 1: slight, 2: mild, 3: moderate, and 4: severe, whereas the cough frequency ranges between 0 (none), 1 (infrequent/occasional), 2 (several times), 3 (many times), and 4 (all the time). Each of the daytime and nighttime scores is calculated by adding the score of cough severity and cough frequency, with a maximum score of 8; the total CDS is an averaged score of daytime and nighttime CDS. All participants will be instructed to record their CDS twice a day: daytime score assessing symptoms occurring from 8am to 8pm and nighttime score from 8pm to 8am. At every visit, a Cough Diary will be given to each participant to record their symptoms until the next visit, and the average score between visits will be used as the outcome to evaluate the efficacy of OJS plus SMS compared with the placebo.

The primary outcome of this trial is the change in CDS between baseline (pre-drug) and week 6 (post-drug) in the OJS plus SMS group compared to the placebo group. CDS was chosen as the primary outcome measure, as a subjective cough score is the most frequently used outcome in clinical trials related to cough ^19^ and was also the primary outcome in our pilot trial showing significant differences between OJS plus SMS and placebo.

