# Statistical analysis

Statistical analysis will be performed by an independent statistician using SAS Analytics Pro software and significance will be accepted at an α-level of 0.05 in a two-sided test. For all data analyses, full analysis (FAS) set will be the primary analysis set in this trial, and a per-protocol (PP) set will be performed as an additional analysis. In this trial, the FAS set included all randomly assigned participants who had been evaluated for efficacy at least once after the administration of the investigational medicine. PP sets were defined as participants who completed the trial without violating the protocol, with compliance lower than 75%, taking prohibited medications, or presenting with serious adverse events. Continuous variables are presented as means and 95% confidence intervals and categorical variables as frequencies and percentages.

For primary efficacy analysis, the changes in CDS between baseline and week 6 of OJS plus SMS compared with placebo will be evaluated using a mixed-effect model repeated measure (MMRM), with each group and visit set as fixed effects and participants as random effects. Secondary efficacy analysis, comparing cough VAS, LCQ-K, GERDQ, HARQ, and EQ-5D-5L evaluated at each visit point with baseline between groups, will also be performed using MMRM. The analysis of the changes in each efficacy outcome within the group will be performed using a paired t-test or Wilcoxon signed-rank test, depending on its normality. For missing values, a multiple imputation will be performed. Additionally, to analyze the trends of CDS over time compared with the baseline, RM-ANOVA will be conducted, and Dunnett’s procedure (based on the baseline) will be used as a multiple comparison correction. A safety analysis will be conducted to compare the number of adverse events between groups using Fisher’s exact test.

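### As listed, the primary MMRM terms (group, visit, participant) give no week-6 treatment contrast, although week 6 is the stated endpoint

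*Protocol*

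**What the plan says.** Three places in the protocol set the target at week 6.

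- Primary efficacy outcome, under Cough symptom score (Cough diary): "The primary outcome of this trial is the change in CDS between baseline (pre-drug) and week 6 (post-drug", comparing the active group with placebo.
- Sample size, Rationale: the calculation was done to "test the difference in the change in CDS from baseline (week 0) to post-dosing of OJS plus SMS (week 6) compared with the placebo".
- Statistical analysis: the primary efficacy paragraph repeats the baseline-to-week-6 change as what is to be evaluated.

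The same paragraph then lists the model: the change in CDS "will be evaluated using a mixed-effect model repeated measure (MMRM), with each group and visit set as fixed effects and participants as random effects". It does not mention a group-by-visit interaction or a contrast at a named visit, and nor does any other section. The secondary outcomes are to be "evaluated at each visit point with baseline between groups, will also be performed using MMRM".

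On timing, the Procedure section states that "participants will visit every 2 weeks until the last follow-up visit on week 8", with dosing for 6 weeks. The timetable has the cough score at weeks 2, 4, 6 and 8 after baseline, so the week-8 value falls after dosing has ended. Each CDS value is the diary average since the preceding visit.

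**The concern.** With group and visit as main effects only, the model holds the difference between arms equal at every visit. Its single treatment estimate is then an average over whichever visits enter, and the week-6 difference is not separately estimated. If the effect builds up over the dosing period, the estimate falls short of the week-6 effect. If an early effect has faded by week 6, the test can be significant with nothing present at the stated time point.

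The secondary plan has the same difficulty more visibly: a model with no interaction cannot produce a separate group comparison at each visit.

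What is at stake is whether the confirmatory test answers the question that the trial was sized for. Two analysts could both follow the protocol in good faith, one with the interaction and one without, and report different primary p-values.

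**Working it through.** **1. The plan's own figure.** Inputs from Sample size: difference 0.75, SD 1.4, power 0.80, two-sided 0.05, dropout 20%.

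n per arm = 2 × 1.4² × (1.960 + 0.842)² / 0.75² = 54.7, so 55. Allowing for dropout, 55 / 0.8 = 68.75, so 69 per arm and 138 in total. This reproduces the protocol and confirms that the trial is sized for the single week-6 contrast. With 55 per arm, power for that contrast is 80.2% by the normal formula and 79.5% by the t-test. The t-test is used below.

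**2. What the listed model estimates.** Take change in CDS at m post-baseline visits, complete data, SD 1.4 at each visit and correlation ρ between visits. The group coefficient in the model without interaction is the mean of the m visit-specific differences. Its standard error is s × √(2/55), where s = 1.4 × √[(1 + (m − 1)ρ)/m].

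- m = 3 (weeks 2–6): s = 1.143, 1.252, 1.303 for ρ = 0.5, 0.7, 0.8.
- m = 4 (weeks 2–8): s = 1.107, 1.232, 1.291.

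**3. Results under assumed profiles.** The protocol gives no time course and no ρ, so every row is an assumption. Power is shown for ρ = 0.5 / 0.7 / 0.8.

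| Assumed difference at weeks 2, 4, 6 (8) | Visits | Average estimated | Power of the averaged test |
|---|---|---|---|
| Gradual: 0.25, 0.50, 0.75 | 2–6 | 0.50 | 62 / 55 / 51% |
| Gradual, fading: 0.25, 0.50, 0.75 (0.50) | 2–8 | 0.50 | 65 / 56 / 52% |
| Faster onset, fading: 0.50, 0.75, 0.75 (0.50) | 2–8 | 0.625 | 84 / 75 / 71% |
| Constant 0.75 | 2–6 | 0.75 | 93 / 88 / 85% |
| Constant 0.75 | 2–8 | 0.75 | 94 / 89 / 86% |
| Early only: 0.75, 0.375, 0 | 2–6 | 0.375 | 40 / 34 / 32% |
| Early only: 0.75, 0.375, 0 (0) | 2–8 | 0.281 | 26 / 22 / 20% |

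In all but the early-only rows the week-6 difference is 0.75, for which the week-6 contrast has 79.5% power. In the early-only rows the week-6 difference is zero, so the figure is the chance of a significant result when nothing is there at week 6. A week-6 contrast would hold that at 5%.

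**4. Simulation.** In 200 simulated trials (gradual profile, weeks 2–6, ρ = 0.7), the model without interaction gave a mean estimate of 0.498 and power of 56.5%. With the interaction, the week-6 contrast gave 0.748 and 81%.

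**5. Other readings of the listed terms.** If only the week-6 change is analysed, there is one visit and no visit effect to fit. If raw CDS at baseline and week 6 are the two visits, the group main effect is (0 + 0.75)/2 = 0.375, half the target. If raw CDS at weeks 0, 2, 4 and 6 is used, even a constant 0.75 becomes 3 × 0.75/4 = 0.5625. None of these recovers the week-6 difference.

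**The case against.** The strongest reply is that the sentence is shorthand. It does not say that group and visit are the only fixed effects, and it does not exclude an interaction. It names the week-6 change as its target, and the next sentence wants secondary comparisons "evaluated at each visit point with baseline between groups". Both aims need visit-specific contrasts, so an interaction was probably intended, and a statistical analysis plan that is not shown here may state it. That stands as to intent. It does not clear the protocol, which names the fixed and random effects itself. The set it names does not deliver its own endpoint, and a later plan that adds the interaction would be extending the listed terms.

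A reader might also infer that the stated 80% power is lost. The documents do not support that. They give no time profile or correlation, and under a constant effect the averaged test has more power than the week-6 contrast. Even with some build-up and fading, power can exceed 80% (84% in the faster-onset row at ρ = 0.5).

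The early-only case shows what the listed model permits. Nothing in the protocol suggests that the effect will vanish during dosing.

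A further temptation is to fault the participant random effect for implying equal variances and correlations across visits, or to require a particular covariance structure, degrees-of-freedom method or treatment of week 8. Those are matters commonly settled in the analysis plan. Nor does the protocol say that week 8 enters the primary model.

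**Conclusion.** The point holds as a mismatch between the listed model and the stated endpoint. It does not establish that the averaged model will be fitted, nor that power will be lost. If the model is fitted as listed, the treatment estimate equals the week-6 difference only under an effect that is constant over visits.

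Against about 80% power for the week-6 contrast, the listed model could have anything from about 51% (gradual onset) to 94% (constant effect) for correlations of 0.5 to 0.8. It could also reject in about 30–40% of trials when an early effect has gone by week 6 and only weeks 2–6 are included, or 20–26% if a null week 8 is added. These figures rest on the assumed profiles, SD 1.4 at every visit, equal correlation between visits and 55 complete participants per arm. The inability to give the planned per-visit secondary comparisons rests on none of these assumptions.

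Because the wording decides the confirmatory test, it should be settled before unblinding.

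**What to change.** In the Statistical analysis section, add the group-by-visit interaction to the fixed effects. State that the primary test is the group contrast at week 6 from that model. Say that the secondary outcomes use the same visit-specific contrasts.

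This takes a sentence or two, no extra data and no change to the 138 participants. The interaction uses a few degrees of freedom. If the effect is truly constant, the week-6 contrast gives up some power relative to the averaged test (79.5% against 85–94% in the table). That is the price of testing the endpoint the protocol names. Covariance structure, degrees of freedom and the handling of week 8 can be left to the statistical analysis plan.

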## Randomization and Blinding

An independent statistician conducted randomization using a computer random number generator of SAS® Version 9.4 (SAS institute. Inc., Cary, NC, USA) using the block randomization method. The allocation ratio was 1:1 for each intervention (OJS plus SMS) and control (placebo) group. The generated random sequence was transmitted to the manufacturer responsible for labeling the participants’ identification codes on each investigational medicine package. These labelled medicines will be delivered to management pharmacists at each hospital, and pharmacists will give the corresponding investigational medicine to each participant using their identification code. The random number will be kept by an independent investigator who has no relationship with the patient throughout the trial and will only be disclosed when a serious adverse event occurs.

All investigators, participants, and outcome assessors will be blinded. The intervention and placebo drugs are distinguished only by the participants’ identification codes, labelled in identical and opaque packages, and both drugs were manufactured with the same color, taste, and smell.

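### The primary MMRM as written gives all visits one common variance and correlation, so the week-6 CDS standard error can be too small if change scores spread out by week 6

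*Protocol*

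**What the plan says.** The Statistical analysis section holds the protocol's only description of the primary model. It names an MMRM for the change in CDS, "with each group and visit set as fixed effects and participants as random effects". It gives no residual covariance structure, no visit-specific variances and no robust standard error. It lists no group-by-visit term and does not say whether week 8 enters the primary model.

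The target is a single time point. Under Cough symptom score (Cough diary): "The primary outcome of this trial is the change in CDS between baseline (pre-drug) and week 6 (post-drug"), compared between arms. Secondary outcomes are "evaluated at each visit point with baseline between groups, will also be performed using MMRM". The test level is fixed: "significance will be accepted at an α-level of 0.05 in a two-sided test".

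The Sample size section gives one standard deviation: "the mean difference between the two groups was found to be 0.75 and the standard deviation was 1.4". No SD or correlation by visit appears anywhere.

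**The concern.** A participant random effect with independent residuals makes the variance identical at every visit and the correlation identical for every pair of visits. Change from baseline often does not behave that way. CDS is averaged over the diary period between visits, so the week-2 period lies closest to baseline and later periods lie further away. If correlation decays with time, the variance of change grows from week 2 to week 6.

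The model would then replace the week-6 variance with an average that includes the less variable early visits. The week-6 interval would be too narrow and its test would reject too often, while the week-2 interval would be too wide. At stake are the nominal 5% level of the primary test in a trial the Background calls confirmatory, and the calibration of the visit-by-visit secondary comparisons.

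**Working it through.** **Inputs from the protocol.** Difference 0.75, SD 1.4 (read as the SD of the week-6 change, since that is what the calculation tests), power 0.8, two-sided level 0.05, dropout 20%, 1:1 allocation, 69 per group, post-baseline visits at weeks 2, 4, 6 and 8.

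**The plan's own figure.** n per group = 2 × 1.4² × (1.960 + 0.842)² / 0.75² = 54.7, rounded up to 55. Then 55 / (1 − 0.20) = 68.75, rounded up to 69 per group and 138 in total. The stated size reproduces, and this point does not affect it.

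**Formulas.** Take complete, balanced data and a random-intercept model with group-by-visit added (an assumption, because the protocol does not list it). Let v_k be the variance of change at visit k.

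- Model SE at week 6 = √(2 × mean(v_k) / n)
- True SE at week 6 = √(2 × v₆ / n)
- Ratio r = √(mean(v_k) / v₆)
- Actual two-sided error = 2 × [1 − Φ(1.96 × r)]

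With n = 55 and SD 1.4, the true SE is 1.4 × √(2/55) = 0.267.

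**Assumption A: equal raw variance, correlation ρ per two-week step.** Then v_k is proportional to 1 − ρ^k, where k counts two-week steps from baseline. For ρ = 0.8, the relative variances at weeks 2, 4, 6 and 8 are 0.200, 0.360, 0.488 and 0.590.

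- Weeks 2, 4, 6: mean 0.349, r = √(0.349/0.488) = 0.846, error 9.7%.
- Weeks 2, 4, 6, 8: mean 0.410, r = √(0.410/0.488) = 0.916, error 7.3%.

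| ρ | r, weeks 2–6 | error | r, weeks 2–8 | error |
| --- | --- | --- | --- | --- |
| 0.6 | 0.881 | 8.4% | 0.927 | 6.9% |
| 0.8 | 0.846 | 9.7% | 0.916 | 7.3% |
| 0.95 | 0.823 | 10.7% | 0.913 | 7.4% |

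Over this range the week-2 SE is overstated by 23–54%. A simulation of 20,000 balanced trials with 55 per arm at ρ = 0.8 agrees: 9.9% and 7.3% with the random intercept, against 5.2% and 5.0% when week 6 has its own variance.

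**Assumption B: SDs of change set directly, with 1.4 at week 6.**

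| SDs by visit | model SE | r | error |
| --- | --- | --- | --- |
| 1.4 / 1.4 / 1.4 | 0.267 | 1.000 | 5.0% |
| 1.2 / 1.3 / 1.4 | 0.248 | 0.930 | 6.8% |
| 1.0 / 1.2 / 1.4 | 0.231 | 0.865 | 9.0% |
| 0.8 / 1.1 / 1.4 | 0.215 | 0.805 | 11.5% |
| 1.0 / 1.2 / 1.4 / 1.4 | 0.241 | 0.901 | 7.8% |
| 1.0 / 1.2 / 1.4 / 1.6 | 0.252 | 0.942 | 6.5% |
| 1.2 / 1.3 / 1.4 / 1.7 | 0.269 | 1.009 | 4.8% |

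**When the direction reverses.** With four visits, the week-6 SE is overstated only if v₈ − v₆ exceeds (v₆ − v₂) + (v₆ − v₄). In the last row, 2.89 − 1.96 = 0.93 exceeds 0.52 + 0.27 = 0.79. A linear or slowing rise in variance does not meet this condition.

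**The case against.** The strongest reply is that covariance structure, degrees of freedom and convergence rules are commonly left to the SAP, which is not shown. The sentence does not say that the participant effect is the sole source of correlation, and a subject effect can sit beside visit-specific residual variances. This stands in part: a reader might infer that the protocol rules out any other structure, and it does not. But the sentence is more than silence, because it states a covariance term. A participant intercept is redundant beside an unstructured residual covariance, so an SAP adopting the usual MMRM covariance would have to depart from the protocol's words.

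A second reply is that the reading is selective. Taken literally for fixed effects too, the model has no group-by-visit term and estimates a visit-averaged effect, which stays near 5% in balanced data. That is correct, but a visit-averaged effect is not the week-6 comparison named as primary. Any model that delivers that comparison needs the interaction, and then the common variance matters.

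A third reply is that growth of variance is not documented. CDS is bounded from 0 to 8, no visit-level SDs are given, and the calculations use complete data rather than the planned multiple imputation with 20% dropout. This stands, and it limits what can be said about size.

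**Conclusion.** The point holds in conditional form. The covariance as stated forces a common variance and correlation, so the week-6 standard error can be too small. It is too small when the week-6 change variance exceeds the average over the modelled visits.

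Under equal raw variance and a correlation of 0.6–0.95 per two-week step, the week-6 SE is 0.82–0.88 of its true value with weeks 2, 4 and 6 modelled (error about 8–11%). With week 8 added it is 0.91–0.93 (error about 7%). These figures assume complete balanced data and a group-by-visit term.

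A reader might infer that the type I error will exceed 5%, or that the SE is too small whenever change scores spread over time. The documents support neither. With equal change variances the error is 5%, and a sufficient jump at week 8 brings it slightly below. The protocol supplies no visit-level figures to decide between these cases. It is still worth correcting before analysis, because the remedy costs almost nothing and removes the dependence on an unverified variance pattern.

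**What to change.** In the Statistical analysis section, replace the participant random effect with an unstructured within-participant covariance across the post-baseline visits, with Kenward-Roger degrees of freedom. Add group-by-visit to the fixed effects, and take the week-6 between-group difference and its interval from that model. Use the same covariance for the secondary outcomes. The fallback order for non-convergence can be left to the SAP.

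The cost is a sentence or two of text and a changed model statement. With four visits there are 4 × 5 / 2 = 10 covariance parameters instead of 2, with negligible loss of precision at about 55 participants per arm. No new data and no change in sample size are needed.

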# Objectives

This study is a randomized, double-blind, placebo-controlled, parallel, multi-center, investigator-initiated clinical trial to assess the efficacy, safety, and economic value of OJS plus SMS compared to placebo in patients with GERC.

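### The supplementary CDS trend analysis and the paired tests ask whether patients changed from baseline, so they cannot answer the drug-versus-placebo question and should be replaced or labelled descriptive (minor)

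*Protocol*

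**What the plan says.** The Objectives section sets out "to assess the efficacy, safety, and economic value of OJS plus SMS compared to placebo in patients with GERC". The Primary Efficacy Outcome section likewise defines the primary outcome as the CDS change to week 6 relative to the placebo group.

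The Statistical analysis section plans four analyses that bear on this:

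- **Primary:** a between-group MMRM of the CDS change to week 6. Group and visit are the only fixed effects named, and participants are random.
- **Secondary:** between-group MMRMs of cough VAS, LCQ-K, GERDQ, HARQ and EQ-5D-5L.
- **Within group:** "The analysis of the changes in each efficacy outcome within the group will be performed using a paired t-test or Wilcoxon signed-rank test", the choice depending on normality.
- **CDS time course:** "to analyze the trends of CDS over time compared with the baseline, RM-ANOVA will be conducted", with Dunnett's procedure referenced to baseline.

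The section's general rule is that "significance will be accepted at an α-level of 0.05 in a two-sided test". It is not restricted to the MMRMs, and the section does not label the last two analyses as descriptive. It does introduce the trend analysis as an addition and the paired tests as within-group.

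**The concern.** The only analysis named for how CDS evolves over time uses each patient's own baseline as the reference. A Dunnett contrast of week 2, 4, 6 or 8 against baseline contains no placebo comparison, and neither does a paired test in one arm. Any improvement common to both arms, such as placebo response or natural course, moves these tests away from their null although the drug does nothing. Dunnett corrects for the number of visits, not for that.

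What is at stake is interpretation. If the MMRM were null, prespecified within-arm p-values on CDS and every other efficacy outcome could still be reported as significant improvement with OJS plus SMS, and nothing in the section warns against reading that as a treatment effect.

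**Working it through.** **Inputs from the protocol.** Sample size section: "the mean difference between the two groups was found to be 0.75 and the standard deviation was 1.4". The same section sets 80% power, 20% dropout and a two-sided 0.05 level. The SD is taken as that of the CDS change from week 0 to week 6, the quantity that section says it sized for.

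**Step 1: the protocol's own figure.** Per arm, n = 2 × (1.960 + 0.842)² × (1.4 / 0.75)² = 54.7, rounded up to 55. With 20% dropout, 55 / 0.8 = 68.75, rounded up to 69, or 138 in total. This matches "we calculated a sample size of 138 (69 participants for each group", so the inputs are read as the protocol meant them. It also gives the range used below: 55 completers to 69 randomised per arm.

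**Step 2: paired test in one arm with an inert drug.** Let both arms improve by the same mean δ. The protocol gives no placebo response, so δ is an assumed range. The paired t statistic is noncentral t with n − 1 degrees of freedom and noncentrality δ / (1.4 / √n). The standard errors are 1.4 / √55 = 0.189 and 1.4 / √69 = 0.169.

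| Shared improvement δ | Noncentrality, n = 55 / 69 | Rejects, n = 55 | Rejects, n = 69 |
|---|---|---|---|
| 0 | 0 / 0 | 5% | 5% |
| 0.1 | 0.53 / 0.59 | 8% | 9% |
| 0.25 | 1.32 / 1.48 | 26% | 31% |
| 0.375 | 1.99 / 2.22 | 50% | 59% |
| 0.5 | 2.65 / 2.97 | 74% | 83% |
| 0.75 | 3.97 / 4.45 | 97% | 99% |

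**Step 3: RM-ANOVA and Dunnett against baseline.** Simulation of one arm: n = 55, weeks 0, 2, 4, 6 and 8, equal correlation between visits, improvement building linearly to week 6 and then level, 4,000 runs, Dunnett critical value 2.46.

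| δ | Time F-test | Dunnett, any visit | Dunnett, week 6 | Between-group test |
|---|---|---|---|---|
| 0 | 5% | 5% | 1% | 4% |
| 0.1 | 8% | 8% | 3% | 5% |
| 0.25 | 21% | 24% | 13% | 4% |
| 0.5 | 75% | 76% | 58% | 5% |
| 0.75 | 99% | 98% | 94% | 5% |

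The last column is a two-sample t-test on the week 0 to 6 change in the same simulated data, standing in for the week-6 MMRM contrast. It stays near 5% because a shared improvement cancels in the difference between arms.

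**The case against.** The strongest reply is that nothing is broken. The primary and secondary efficacy comparisons are between-group MMRMs, so the objective is met and their type I error is untouched. The paired tests and the trend analysis are presented as within-group and additional. Rejecting no change when patients did change is a correct rejection, so the high percentages above are power for a real change over time, not error rates. They become misleading only if read as a drug effect, which the protocol does not plan. All of this stands, and it makes the point minor.

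It does not remove the point. The trend analysis is on the primary outcome, it is the only one named for the time course, and a placebo-referenced version is available from the same data.

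A reader might also infer stronger faults that the document does not support:

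- **That any placebo response makes these tests reject.** At 0.1 points rejection is only 8–9%. It nears certainty only around 0.75.
- **That regression to the mean is built in by selection.** Entry requires cough for more than 8 weeks but no minimum CDS, so patients are not selected on the outcome score.
- **That the plan's multiplicity control is used up on the wrong family.** Dunnett adjusts within its own set of visits and takes nothing from the primary, a single contrast at week 6.
- **That Dunnett is too liberal even for its own question.** With a pooled error term and AR(1) correlation its familywise error is about 7–10%, but under equal correlation it is about 5%. The protocol states neither the error term nor the correlation, and such detail may sit in the SAP. This is a conditional side note.

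**Conclusion.** The point holds as a minor one. The RM-ANOVA with Dunnett and the paired tests address change from baseline and cannot show a drug effect. With an inert drug, the paired test in one arm rejects in 26–31% of trials at a shared improvement of 0.25 points and in 97–99% at 0.75, the size of the planned treatment difference. The trend tests behave similarly.

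These figures assume an SD of change of 1.4, 55 to 69 patients per arm, a shared improvement that the protocol does not supply and, for the trend tests, equal correlation and analysis within one arm. They apply to CDS only; no size is claimed for the other scales. The trial's confirmatory inference is not affected, and the document does not support saying that an efficacy claim will be drawn from these tests.

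**What to change.** **CDS time course.** Replace the RM-ANOVA/Dunnett sentence with: *The time course of CDS will be described by the OJS plus SMS minus placebo difference in change from baseline at weeks 2, 4, 6 and 8, with 95% confidence intervals, from the MMRM including a group-by-visit term; differences at visits other than week 6 are supportive.* The interaction has to be written in: with only group and visit as fixed effects, the model yields one common group difference and no visit-specific ones.

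**Within-group changes.** Replace the paired-test sentence with: *Within-group changes will be presented as means with 95% confidence intervals, are descriptive, and will not be used to claim efficacy.* The label matters because an interval that excludes zero carries the same message as a significant paired t-test.

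**Cost.** Two sentences in the protocol or SAP. No new data or patients are needed, and there is slightly less analysis. The sponsor gives up the within-arm p-values.

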3. EKG
4. Laboratory tests

For the safety outcomes, vital signs (blood pressure, body temperature, pulse rate, and respiratory rate), adverse events, and laboratory test will be evaluated during the trial period. At every visit, vital signs and adverse events will be assessed, and laboratory tests will be conducted before and after drug administration. Liver function tests (aspartate aminotransferase, alanine aminotransferase, alkaline phosphatase, gamma-glutamyl transferase, bilirubin, and protein/albumin), renal function tests (blood urea nitrogen and creatinine), electrolyte content (sodium, potassium, and chloride), blood coagulation tests (prothrombin time and activated partial thromboplastin time), and complete blood count will be performed. Adverse events will be collected by asking participants whether any unfavorable and unintended signs, symptoms, or diseases presented after taking the investigational medicine. These will then be assessed for severity and causality of investigational drugs, and investigators will follow up until the adverse events end.

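### As worded, Fisher's exact test is applied to the number of adverse events, although one participant can contribute several; the unit should be participants with at least one event (minor)

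*Protocol*

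**What the plan says.** The Protocol gives one sentence on the safety comparison, at the end of Statistical analysis: "A safety analysis will be conducted to compare the number of adverse events between groups using Fisher’s exact test". The same section sets the level for all tests: "significance will be accepted at an α-level of 0.05 in a two-sided test". The operative words, "compare the number of adverse events between groups using", name the event as the unit. The Protocol nowhere restates it as participants with an event and gives no denominator for the table. This is the only between-group safety test it names.

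Under Safety Outcomes, collection is repeated: "At every visit, vital signs and adverse events will be assessed". The schedule marks adverse events at visits 2 to 6, that is, weeks 0, 2, 4, 6 and 8.

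Elsewhere the Protocol does count participants. The second reason for discontinuing the trial, under Dropout and Early termination criteria, is a percentage of all participants with a related moderate or severe event.

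**The concern.** Fisher's exact test works on a two-by-two table in which every independent unit is classified once, as having the outcome or not. Participants with or without an adverse event fit that table. Events do not: nothing corresponds to a non-event, a group's count can exceed its number of participants, and several events from one participant are correlated. The test treats them as separate independent observations, so it can understate the variability of the count.

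At stake is the p-value of the only named between-group safety test. A few participants with many events could produce an apparent difference where the same number of people were affected in each arm, or hide a real one. A second, practical risk is that the sentence cannot be carried out without choosing a denominator, and that choice could be made after the data are seen.

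**Working it through.** **Arm size, reproduced from the Protocol.** Under Sample size: "the mean difference between the two groups was found to be 0.75 and the standard deviation was 1.4"; power 0.8; two-sided 0.05; 20% dropout.

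n = 2(z₀.₉₇₅ + z₀.₈₀)² × SD² / difference² = 2 × (1.960 + 0.842)² × 1.4² / 0.75² = 54.7, so 55 per arm. Allowing for dropout, 55 / (1 − 0.20) = 68.75, so 69 per arm and 138 in total. This matches the Protocol, and 69 per arm is used below.

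**One constructed example.** Suppose 10 of 69 participants in each arm have an adverse event, giving 10 events in one arm and, through repeats, 22 in the other.

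- Participants, 10/69 against 10/69: p = 1.0.
- Events, 10/69 against 22/69: p = 0.026.

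Incidence is identical, yet the event-level test is significant at 0.05.

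**False-positive rate with no true difference.** The documents give no adverse event rate, so the rates here are assumptions. Each participant is affected with a fixed probability, equal in both arms. An affected participant has 1 + Poisson(m − 1) events, so m is the mean number of events per affected participant. Fisher's exact test is two-sided at 0.05, with events counted out of 69. There were 4,000 simulated trials per row for m up to 1.2 and 10,000 for the last three rows.

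| Participants affected | Mean events each (m) | Events out of 69 |
| --- | --- | --- |
| 20% | 1.0 | 0.030 |
| 5% | 1.2 | 0.036 |
| 10% | 1.1 | 0.044 |
| 20% | 1.1 | 0.059 |
| 10% | 1.2 | 0.062 |
| 20% | 1.2 | 0.078 |
| 20% | 1.5 | 0.150 |
| 20% | 2 | 0.251 |
| 15% | 3 | 0.378 |

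On participants with at least one event, the same test rejects in about 3% of trials or fewer. It stays below 5% because the test is conservative.

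**Other event-level tables.** The Protocol gives no denominator, so two alternatives were tried on the last three rows.

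- Events over participant-visits (4 post-dose visits × 69 = 276): about 0.10, 0.19 and 0.28.
- Events against event-free participants: about 0.10, 0.16 and 0.22.

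Both inflate, but less than events out of 69.

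**A second event model.** Events per participant were Poisson (no clustering) or negative binomial (clustered, dispersion k = 1, 0.5 or 0.25), with 10,000 trials each.

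- Mean 0.2 to 0.3 events per participant, events out of 69: 0.055 to 0.076 without clustering, 0.083 to 0.24 with it.
- Mean 0.5, events out of 69: 0.13 to 0.38.
- Mean 0.8: the count exceeds 69 in at least one arm in 6% to 31% of trials, so that table cannot be formed.
- Participant-visit table without clustering: 0.036 to 0.050 for means up to 0.5, so no inflation.
- Participant-level test: 0.028 to 0.036 throughout.

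**The case against.** The strongest reply is that the sentence is shorthand. Fisher's exact test needs a two-by-two table, and the only natural one here is participants with and without an event. The plan to summarise categorical variables by frequency and percentage, and the participant-based discontinuation rule, both fit that reading. Safety tables are also commonly specified in a statistical analysis plan, which may exist and is not shown. The consequences are limited: the test carries no confirmatory claim, the discontinuation rule uses no p-value, each event is still assessed for severity and causality, and the participant-level table can be produced from the same data at any time.

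Much of this stands. The wording may be loose, the breakdown by type or relatedness can be left to the analysis plan, and the point is minor. It does not remove the point, because the Protocol does not leave the unit open. It names both the test and the unit, and the two do not fit; a correct analysis plan would have to depart from the sentence.

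A reader might go further and infer that the safety p-value is bound to be wrong, or that false signals are to be expected. The documents do not support that. They give no event rates, the error disappears if each participant has at most one event, and it is small or absent when repeat events are few.

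**Conclusion.** The sentence is wrong as written, and the defect is minor. An event-level Fisher test has no valid non-event count and uses units that are not independent, because one participant can contribute several events over the visits to week 8.

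With 69 per arm and events out of 69, the false-positive rate ranges from about 0.03 to 0.06 when repeat events are few to about 0.15 to 0.38 with 1.5 to 3 events per affected participant. The participant-level test gives about 0.03 or less. That range rests on assumed event rates and on one of several possible tables. That the unit does not suit the test follows from the text alone; how much this matters in practice depends on how often participants report repeat events. Neither the primary endpoint nor the sample size is affected.

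**What to change.** In Statistical analysis, replace the unit: Fisher's exact test compares, between groups, the number of participants with at least one adverse event, out of the participants in the safety analysis in each group. Add that the total number of events per group is reported descriptively. A count model for events is optional and is not needed to correct the sentence.

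The cost is one sentence. Data collection, visits and sample size do not change. The change should be made before unblinding, so that the unit is not chosen with the results in view.
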